### Strategies to Enhance Engagement

To maximize caregiver engagement with iCURE, we will implement 4 strategies: (1) during registration, caregivers will be instructed to disable the “Do Not Disturb” mode in their WeChat service account; (2) caregivers in the intervention group will earn lottery entries for completing questionnaires and digital points for viewing educational materials, with both entries and points available to be redeemed in ranking competitions, as supported by prior research [28,50] and findings from a needs assessment; (3) safety-themed activities will be organized on designated special days, such as World Drowning Prevention Day, to reinforce injury prevention knowledge; and (4) iCURE materials will be shared through existing WeChat groups by teachers and health care providers in intervention areas to leverage community networks and expand outreach.

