Injury risk assessment: a comprehensive child injury risk assessment questionnaire, developed based on validated tools [43-47], to assess child age, caregiver and child behaviors, and environmental risk.Instant feedback: upon completing the risk assessment, participants receive immediate feedback and tailored recommendations generated by an integrated expert classification system and a decision tree model. This system stratifies children into low or moderate risk or high risk, which supports further personalized prevention strategies. For research purposes, participants who are randomly assigned to the control group will complete the assessment but will not receive feedback. Caregivers of children in the intervention group who are identified by the system as “high risk” will receive item-specific risk reports. This individualized risk profile will guide the dissemination of AI-tailored education materials for each child.Injury reporting: caregivers are encouraged to report any injury events their children experienced during the study period. The module facilitates timely documentation and monitoring of injury events.Interactive questions and answers (Q&A): caregivers may submit injury prevention questions through the platform’s real-time Q&A interface, which provides instant computer-generated and automated responses. The iCURE platform uses a hybrid natural language processing approach that combines keyword matching and text similarity analysis to retrieve and deliver relevant, automated responses from a curated injury prevention knowledge base created by the research group.Tailored education: personalized educational content on child injury prevention is delivered in various formats (eg, text, images, long-form infographic post, flyers, and short videos). Delivery frequency is determined by a rule-based decision logic algorithm and tailored to the child’s risk level; caregivers of low-risk children receive content once per week, while those with higher-risk children receive it 2 or 3 times per week.

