### Implementation Protocol

During routine consultations, primary health care providers will assist caregivers in registering for the iCURE WeChat service account. Upon registration, all caregivers will complete a questionnaire providing demographic information, their child’s injury history, and an injury risk assessment survey.

Caregivers randomly assigned to the intervention group will then receive the full version of the iCURE program, including real-time feedback, tailored educational content, and access to the Q&A module. The control group will access a simplified version involving completion of assessment surveys that are used only for data collection; they will receive no feedback, education, or supplemental materials. Both groups will continue to receive routine safety education provided by preschool teachers and primary health providers. Group allocation is detailed in Table 1. Details regarding the timeline for recruitment and intervention period are shown in Figure 3.

**Table 1. T1:** Functions of iCURE (Intelligent Child Unintentional-Injury Reduction & Education) used by intervention group and control group.

Functions	Intervention group	Control group
Data collection	✓	✓
Injury risk assessment	✓	✓^a^
Instant feedback	✓	
Tailored education	✓	
Interactive questions and answers	✓	

a Control group will complete the injury risk assessment for data collection purposes, with no risk evaluation reports provided.

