### Data Collection

Primary outcome data will be collected every 3 months to minimize recall bias. Secondary outcomes, which are less sensitive to recall bias, will be assessed annually. The baseline survey includes demographic information, child injury history over the past 12 months, caregiver supervision behaviors, and injury risk assessment, selected based on established associations with child injury and potential confounders [51]. All data will be self-reported, collected via the internet-based iCURE system, and securely stored on encrypted databases and hard drives. Caregivers will receive automated reminders followed by telephone follow-up if necessary to improve response rates.

The iCURE system will automatically record user engagement indicators, including (1) whether educational content was viewed, (2) frequency and duration of viewing, (3) messages to iCURE research team, and (4) online subscription to the iCURE WeChat service account.

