### Data Analysis

Data will be analyzed following intention-to-treat principles and including all participants as originally assigned, regardless of adherence. Descriptive analysis (mean, SD, median, IQR, and proportion) will be used to describe baseline characteristics by groups. Differences in unintentional injury incidence across 5 timepoints (baseline, 3, 6, 9, and 12 mo) and other outcomes at 2 timepoints (baseline and 12 mo) will be examined using rank-sum tests for ordinal outcomes, chi-square tests for categorical outcomes, and independent 2-sample *t* tests for continuous outcomes. Within-group changes over time will also be evaluated.

Generalized linear mixed models with a Poisson link function will be used to compare the 12-month injury incidence between groups, adjusting for baseline covariates and accounting for clustering at the street or town level. Risk ratios and 95% CIs will be reported. Generalized estimating equations will also be used to assess repeated measures of injury incidence across follow-up timepoints, providing population-averaged estimates while accounting for within-subject and within-cluster correlations. Secondary outcomes, including changes in injury risk levels and caregiver supervision behaviors, will be analyzed using regression models appropriate to the type and distribution of the variable. User engagement indicators will be included as covariates of the effectiveness analysis model.

Two sets of sensitivity analyses will be performed to assess the robustness of findings: (1) per-protocol analyses and (2) models excluding participants with missing primary outcome data. Missing data will be documented and addressed using appropriate statistical methods as needed.

This study will adhere to the CONSORT (Consolidated Standards of Reporting Trials) 2025 [52] statement to perform data analysis and report results.

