### Ethical Considerations

This study was reviewed and approved by the Ethics Committee of Xiangya School of Public Health, Central South University (XYGW-2024-71). All participants will provide electronic informed consent via the iCURE WeChat service account prior to participation, in accordance with national and institutional ethical guidelines. To ensure privacy and confidentiality, all data will be securely stored on encrypted databases and password-protected hard drives. Data will be de-identified before analysis, and no personally identifiable information will be retained in the analytic dataset. Participants will receive a modest digital monetary incentive ranging from 5 to 50 Chinese Yuan through a lottery-based mechanism via WeChat for their time and participation. No identifiable information will be included in the manuscript or any supplementary materials.

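### The engagement section gives lottery entries for completing questionnaires to the intervention arm, while the ethics section gives a lottery to participants in general; since these questionnaires carry the primary outcome, response could differ by arm

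*Protocol article*

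**What the plan says.** Strategies to Enhance Engagement, item 2, states that "caregivers in the intervention group will earn lottery entries for completing questionnaires and digital points for viewing educational materials". It describes no equivalent for controls.

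Ethical Considerations states that "Participants will receive a modest digital monetary incentive ranging from 5 to 50 Chinese Yuan through a lottery-based mechanism via WeChat", as recognition of time and participation, and names no arm.

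Implementation Protocol describes what controls receive: "The control group will access a simplified version involving completion of assessment surveys that are used only for data collection". No reward is mentioned there.

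Data Collection makes these surveys the outcome instrument: "All data will be self-reported, collected via the internet-based iCURE system", and "Primary outcome data will be collected every 3 months to minimize recall bias". The same section adds, without limiting it to one arm, that "Caregivers will receive automated reminders followed by telephone follow-up if necessary to improve response rates".

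On missing outcomes, Data Analysis says that "Missing data will be documented and addressed using appropriate statistical methods as needed", and lists a model without participants whose primary outcome is missing as a sensitivity analysis. Outcomes defines the primary outcome as children with an injury over the 12 months, divided by the total number of children.

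**The concern.** Rewarding caregivers for viewing education is part of the intervention and properly belongs to one arm. Rewarding them for returning the outcome questionnaire is part of measurement and should be the same in both arms. Item 2 joins the two rewards and assigns both to the intervention group. Item 1 of the same list speaks of caregivers generally, so the restriction in item 2 does not read as a slip of style.

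The outcome is sensitive to this. It rests on caregiver report and includes minor events treated by a family member or teacher. The Discussion accepts that some minor injuries may go unreported. If one arm has a stronger reason to respond, the arms can differ in the share of injuries captured, and the risk ratio then mixes the effect of iCURE with the effect of the incentive. Injuries that were never reported cannot be recovered from the data at the analysis stage without assumptions.

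**Working it through.** **1. The two sections side by side.** There are two ways to read them together.
- They describe one lottery. Then they disagree on who is in it.
- The ethics section describes a payment to both arms and item 2 describes an additional scheme. Then there is no contradiction, but the intervention arm still has an extra reward for completing questionnaires.

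Both readings call for a correction or a clarifying sentence.

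**2. The plan's own figure.** Inputs from Sample Size: control incidence 15.5%, 25% relative reduction (so 0.155 × 0.75 = 0.11625), design effect 1.5, loss 30%, power 80%, alpha .05 (taken as two-sided). The usual formula for two proportions gives 1225 per arm. Then 2 × 1225 × 1.5 = 3675, and 3675 / (1 − 0.30) = 5250. The article states 5178, and 5250 is 1.4% above that, so the figure is reproduced closely enough. It does not depend on the incentive. It shows that one loss rate was planned for both arms.

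**3. What unequal loss could do at worst.** The documents give no loss by arm. Assume 25% in intervention and 35% in control, which average the planned 30%, and count unreturned surveys as no injury. Then

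observed RR = true RR × f(intervention) / f(control),

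where f = 1 − loss if all loss occurs at the start, and f = 1 − loss/2 if it is spread evenly over the year.

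| True RR | Loss at start | Loss spread evenly |
|---|---|---|
| 0.75 | 0.75 × 0.75 / 0.65 = 0.865 | 0.75 × 0.875 / 0.825 = 0.795 |
| 1.00 | 0.75 / 0.65 = 1.15 | 0.875 / 0.825 = 1.06 |

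**4. The same question by quarterly survey.** Assume four surveys, constant hazard, quarterly risk q = 1 − (1 − p)^(1/4), response probability r per survey, and unanswered surveys counted as no injury. The observed 12-month risk is 1 − (1 − r·q)^4. Control incidence is 15.5% and intervention response is fixed at 90%.

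| Control response | Observed RR, true 0.75 | Observed RR, true 1.00 |
|---|---|---|
| 90% | 0.749 | 1.00 |
| 85% | 0.790 | 1.06 |
| 80% | 0.837 | 1.12 |
| 70% | 0.951 | 1.27 |

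At a control incidence of 9%, close to the reported baseline, a true 0.75 gives 0.749, 0.792, 0.840 and 0.957. With equal response the designed effect comes back almost exactly.

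**5. Different handling, different answer.** Suppose non-responders are excluded and, within each arm, loss is unrelated to injury. Numerator and denominator in each arm are then both multiplied by the same f, which cancels. The observed RR is 0.75 even with the 25%/35% split. If response is related to injury, the estimate can move either way.

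**The case against.** **Item 2 does not exclude controls.** It lists ways to raise engagement and may be loosely worded, while the ethics section is the general statement on payment. This stands: that only the intervention arm is rewarded is an inference. It does not dispose of the point, because item 2 names one arm for a reward attached to the outcome instrument.

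**No difference has been shown.** The 87.2% (5842/6701) is pooled, the prizes are modest (5 to 50 Yuan), and reminders and calls go to caregivers generally. This also stands. It limits the point to a risk in the design.

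**The figures are a worst case.** The loss split is assumed, and 30% is a planning figure that the authors themselves call very conservative. Counting unreturned surveys as no injury is compatible with the stated denominator, but Data Analysis treats missing outcomes as missing. This stands.

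**A stronger reading.** A reader might infer that the trial is biased toward no effect. The documents do not support a direction. The lottery entry rewards completion, not the report of an injury, and the result turns on missing-data handling and on who responds.

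**The injury-reporting module.** A reader might also infer that it adds further unequal ascertainment, since "caregivers are encouraged to report any injury events their children experienced during the study period" at any time. The text does not support this. That sentence names no arm, although the neighbouring description of feedback does. Data Collection and Data Analysis tie the primary outcome to 3-monthly collection, and nothing says that module reports count toward it.

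**Conclusion.** The point holds as an inconsistency in the text with a consequence for the primary outcome. One section assigns a reward for completing questionnaires to the intervention arm, another describes a lottery for participants at large, and the questionnaires concerned supply the primary outcome. If the engagement section is followed as written, response and ascertainment may differ by arm.

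The size is not known. With the assumed 25%/35% loss and unreturned surveys counted as no injury, a true 0.75 would appear as about 0.80 to 0.87. With non-responders excluded and loss unrelated to injury within arm, it would stay at 0.75. These values mark out a sensitivity range and do not estimate bias in this trial. That the article names no missing-data method is not part of the point, since an article commonly leaves that to the analysis plan.

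**What to change.** 1. Reconcile Strategies to Enhance Engagement with Ethical Considerations. State that incentives for completing questionnaires are identical in both arms for all remaining waves, and keep only the points for viewing education in the intervention arm.
2. State what each arm was in fact offered at the waves already collected.
3. Report questionnaire completion by arm at every wave, including the first follow-up now given only as a total.
4. If incentives did differ at earlier waves, prespecify a sensitivity analysis that lets missingness depend on arm. Changing the incentive later cannot repair data already gathered.

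If controls already receive the same lottery, the change is a sentence or two of text. If not, the cost is a short amendment, prizes of 5 to 50 Yuan in the control arm, and a change in control-arm incentives during follow-up, which should be dated and reported. The sample size is unaffected.

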### Data Collection

Primary outcome data will be collected every 3 months to minimize recall bias. Secondary outcomes, which are less sensitive to recall bias, will be assessed annually. The baseline survey includes demographic information, child injury history over the past 12 months, caregiver supervision behaviors, and injury risk assessment, selected based on established associations with child injury and potential confounders [51]. All data will be self-reported, collected via the internet-based iCURE system, and securely stored on encrypted databases and hard drives. Caregivers will receive automated reminders followed by telephone follow-up if necessary to improve response rates.

The iCURE system will automatically record user engagement indicators, including (1) whether educational content was viewed, (2) frequency and duration of viewing, (3) messages to iCURE research team, and (4) online subscription to the iCURE WeChat service account.

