Recognizing the potential of digital health as an alternative to deliver health-related messaging to parents and families, both the WHO and China’s national health strategies have emphasized the importance of integrating mobile health (mHealth) into public service delivery [13-15]. By leveraging digital technologies, mHealth can bridge gaps between research and practice by overcoming geographical and temporal barriers to deliver scalable, cost-effective interventions, including to resource-limited settings [16].

Further, the rapid advancement of artificial intelligence (AI) technologies has made it increasingly feasible to design interventions that integrate AI into mHealth apps. AI-enabled systems can ease workforce shortages by providing real-time support and interactions, automated risk assessments, and personalized recommendations. For example, a randomized controlled trial reported that an AI-powered digital platform for lifestyle change was effective in supporting weight loss among adults [17].

mHealth apps for child injury prevention have been piloted in high-income countries such as the United States [18-22], South Korea [23,24], and Australia [25], as well as in China [26-30]. Most of these interventions focus on delivering educational content via mobile platforms. However, several limitations have restricted their broader application in China [18-30]: (1) they primarily target preschool-aged children ages 3‐6 years, overlooking risk among infants and toddlers [18,19,21,24,27-30]; (2) they rely on standalone applications, creating limited user engagement and poor long-term adherence [18-29]; and (3) they typically require dedicated technical support, continuous user assistance, specialized intervention skills, and localized cultural and linguistic appreciation, infrastructure that is not embedded within the National Basic Public Health Service Program. Together, these limitations undermine scalability, sustainability, and integration into routine service delivery in China [18-30].

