### Participant Recruitment

A 2-stage recruitment strategy will be conducted. First, 12 streets and towns were selected from 5 administrative districts in Changsha, including 3 urban districts (Kaifu, Yuhua, and Yuelu) and 2 rural areas (Ningxiang and Liuyang). Each district consisted of at least 2 streets and towns that were eligible for study recruitment (Figure 1). Eligible streets and towns had a primary health care institution present that (1) provides basic public health services for a population with over 2000 children younger than 5 years of age and (2) reports they are not involved in any active child injury prevention programs.

One health care provider per institution will facilitate participant recruitment through (1) face-to-face communication, leaflet distribution, and poster display during routine services; (2) digital advertisements and instructional videos shared through established communication platforms, such as WeChat groups; and (3) collaboration with local schools serving children aged 3 to 5 years, where teachers will distribute flyers to caregivers.

Families will be eligible if children (1) are aged ≤5 years at the time of baseline survey; (2) live with a primary caregiver who provides daily support; (3) reside in the selected study site; (4) have a caregiver aged ≥18 years who is literate, owns a smartphone, and provides informed consent; and (5) are not enrolled in other structured injury prevention programs. Children with severe illnesses requiring specialized care or hospitalization will be excluded.

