## Results

The study received funding in January 2023. Participant enrollment began in August 2024 and was completed in February 2025. A total of 6701 individuals completed baseline data, with 3110 allocated to the intervention group and 3591 to the control group (Table 2). The two groups somewhat differed in child age, place of residence, caregiver’s age, and education—the control group had higher proportions of children aged 3 to 5 years (69.7% vs 57.6%), residing in urban areas (61.3% vs 57.4%), caregivers aged 30 years and older (81.2% vs 74.9%) and receiving high or vocational school education and higher (85.7% vs 80.2%) than the intervention group (*P*<.05). The baseline 12-month injury incidence reported by caregivers was 8.86% (7.96-9.84) in the control group and 9.04% (8.06-10.11) in the intervention group.

By May 2025, 5,842 (87.2%) participants had completed the first follow-up survey.

**Table 2. T2:** Number of recruited caregivers and children by demographic characteristics (%).

Variables	Overall, n (%)	Control, n (%)	Intervention, n (%)	*P* value
Total	6701 (100.0)	3591 (100.0)	3110 (100.0)	
Child gender				>.99
Girl	3147 (47.0)	1686 (47.0)	1461 (47.0)	
Boy	3554 (53.0)	1905 (53.0)	1649 (53.0)	
Child age (years)				<.001
1	1047 (15.6)	468 (13.0)	579 (18.6)	
1-2	1358 (20.3)	619 (17.2)	739 (23.8)	
3-5	4296 (64.1)	2504 (69.7)	1792 (57.6)	
Place of residence				.001
Urban	3988 (59.5)	2203 (61.3)	1785 (57.4)	
Rural	2713 (40.5)	1388 (38.7)	1325 (42.6)	
Caregiver’s gender				.09
Female	5400 (80.6)	2922 (81.4)	2478 (79.7)	
Male	1301 (19.4)	669 (18.6)	632 (20.3)	
Caregiver’s age (years)				<.001
＜30	1458 (21.8)	677 (18.9)	781 (25.1)	
30-39	4343 (64.8)	2408 (67.1)	1935 (62.2)	
≥40	900 (13.4)	506 (14.1)	394 (12.7)	
Number of children in the family				.51
1	3010 (44.9)	1627 (45.3)	1383 (44.5)	
≥2	3691 (55.1)	1964 (54.7)	1727 (55.5)	
Caregiver’s education				<.001
Junior high school or lower	1131 (16.9)	514 (14.3)	617 (19.8)	
High or vocational school	1493 (22.3)	816 (22.7)	677 (21.8)	
College or higher	4077 (60.8)	2261 (63.0)	1816 (58.4)	

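### The baseline 12-month injury incidence includes infants who have not lived 12 months, so it is mislabelled, slightly understated and an uneven start for the planned baseline-to-follow-up comparisons

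*Protocol article*

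**What the plan says.** Under Participant Recruitment, children qualify if they "are aged ≤5 years at the time of baseline survey"; no minimum age is given. Infants are wanted: the Introduction faults earlier programmes for "overlooking risk among infants and toddlers".

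Under Data Collection, the baseline survey records "child injury history over the past 12 months". The same window applies to every child, and no rule is given for those younger than the window.

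The Results report recruitment "with 3110 allocated to the intervention group and 3591 to the control group" and state: "The baseline 12-month injury incidence reported by caregivers was 8.86% (7.96-9.84) in the control group and 9.04% (8.06-10.11) in the intervention group". Table 2 gives three age rows, printed 1, 1-2 and 3-5 years. The first holds 1047 children: 468 control and 579 intervention.

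Under Data Analysis, baseline is one of the compared occasions: "Differences in unintentional injury incidence across 5 timepoints (baseline, 3, 6, 9, and 12 mo" and so on. Change within each group is also to be evaluated. The primary model is described as "adjusting for baseline covariates and accounting for clustering at the street or town level"; the covariates are not listed.

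**The concern.** A child of seven months cannot have a 12-month injury history. The caregiver's answer is true for the time since birth, but it enters a figure labelled as covering 12 months. About one child in six appears to be in this position, and the share differs between arms.

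The label matters because the plan uses the baseline figure as a starting point. The primary outcome covers a full 12 months of follow-up for every child. Setting it against a baseline that covers 0 to 11 months for infants builds in a rise that has nothing to do with the intervention. The rise is larger in the arm with more infants, so comparing change between arms would tilt slightly against the intervention. Matching the nominal length of the baseline and follow-up windows would not remove this, because the infants' baseline window is short whatever it is called.

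**Working it through.** **1. Who is in the youngest row.** The age rows sum to the arm totals: 468 + 619 + 2504 = 3591 and 579 + 739 + 1792 = 3110. A row for age 1 followed by a row for 1-2 would overlap, so the first row most plausibly means under 1 year, with a lost less-than sign. Shares: 468/3591 = 13.0%, 579/3110 = 18.6%, 1047/6701 = 15.6%.

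**2. Are they in the reported incidence?** Event counts are not printed, so I back-calculated them.

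- All children: 318/3591 = 8.86% and 281/3110 = 9.04%. Wilson score intervals with continuity correction are 7.96-9.84 and 8.06-10.11, which match the article exactly.
- Youngest row removed: the denominators are 3591 - 468 = 3123 and 3110 - 579 = 2531. The nearest counts give 277/3123 = 8.87% (7.91-9.93) and 229/2531 = 9.05% (7.97-10.25). Neither interval matches. The printed percentages cannot be reached either: one event fewer gives 276/3123 = 8.84% and 228/2531 = 9.01%.

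So the youngest children are counted in full.

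**3. Size of the understatement.** The documents give neither injuries by age nor infants' ages in months, so this step rests on assumptions. Let s be the infant share, e the mean infant look-back in years, and r the infants' full-year risk relative to older children.

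- Older children's incidence: q = observed / [(1 - s) + s·r·e]
- Full-window incidence: F = q × [(1 - s) + s·r]

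Middle case, e = 0.5 and r = 0.5:

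- Control: q = 8.86 / (0.8697 + 0.1303 × 0.25) = 9.82; F = 9.82 × (0.8697 + 0.1303 × 0.5) = 9.18%.
- Intervention: q = 9.04 / (0.8138 + 0.1862 × 0.25) = 10.51; F = 10.51 × (0.8138 + 0.1862 × 0.5) = 9.53%.

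| e | r | Control F (shift) | Intervention F (shift) | Gap |
|---|---|---|---|---|
| 0.75 | 0.25 | 8.94 (+0.08) | 9.16 (+0.12) | 0.22 |
| 0.5 | 0.5 | 9.18 (+0.32) | 9.53 (+0.49) | 0.35 |
| 0.5 | 1.0 | 9.48 (+0.62) | 9.97 (+0.93) | 0.49 |
| 0.25 | 1.0 | 9.82 (+0.96) | 10.51 (+1.47) | 0.69 |

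The reported gap is 9.04 - 8.86 = 0.18 points.

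**4. Effect on change from baseline.** The shift in each arm is the artificial rise to 12 months. The excess in the intervention arm runs from 0.12 - 0.08 = 0.04 to 1.47 - 0.96 = 0.51 points.

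**5. Against sampling error.** The standard error of the reported gap, ignoring clustering, is √(0.0886 × 0.9114/3591 + 0.0904 × 0.9096/3110) = 0.70 points. Even the largest gap in the table, 0.69, is about one standard error.

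**The case against.** The strongest reply is that no confirmatory result depends on this look-back. The primary outcome is prospective, with the same planned 12 months for every child. The generalized estimating equations run across follow-up occasions, and the sample size does not use the baseline survey. All of that stands. The within-group evaluation is supplementary, and children age a year between the two windows, so it could not carry a causal reading anyway. Nor is the age imbalance hidden: the Results mention it and Table 2 shows it with P<.001.

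A reader might infer three stronger things that the documents do not support.

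- **That a prior-injury covariate in the primary model is wrong.** The article never names prior injury as a covariate. Data Collection says only that the baseline items were chosen as correlates of injury and potential confounders, so its use is likely but not stated, and its coding is not given. A shortened history recorded before treatment would weaken the adjustment but would not by itself bias the randomised comparison.
- **That the true baseline difference is two to three times the reported one.** This holds only if infants are injured at the same rate per unit time as older children. In that case, with a mean look-back of 0.5 year, the ratio moves from 9.04/8.86 = 1.02 to 9.97/9.48 = 1.05. With √(1/318 + 1/281) = 0.082 as the standard error of the log ratio, the 95% interval is about 0.90 to 1.24 before clustering. If infants' risk is lower, the gap barely moves.
- **That the baseline answers are false.** They are correct for time since birth; the window is truncated.

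What the reply does not remove is that the article itself admits infants, fixes one 12-month window, labels the pooled figure accordingly and schedules comparisons against it.

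**Conclusion.** The point holds in a limited form. The baseline figures are labelled as 12-month incidence but mix full and partial windows. They understate a full-year incidence by about 0.1 to 1.0 points in control and 0.1 to 1.5 points in intervention. The between-arm gap of 0.18 points would become about 0.2 to 0.7, which does not show a real baseline difference. The practical consequence is confined to the baseline description and to the planned baseline-to-follow-up and within-group comparisons.

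The sizes rest on three assumptions: that Table 2's first row means under 1 year, that infants' mean look-back is 0.25 to 0.75 year, and that their full-year risk is 0.25 to 1.0 times that of older children. The direction does not depend on the last two within those ranges.

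**What to change.** - Define the baseline window as the past 12 months, or since birth if the child is younger.
- Report baseline injury per child-time, with the smaller of age and 12 months as each child's denominator, or report it by age band.
- Make baseline-to-12-month and within-group comparisons on child-time, or restrict them to children aged 12 months or more at baseline.
- If prior injury is used as a covariate, put age, or an interaction with being under 12 months, in the same model.
- Correct the label of Table 2's first age row if it should read under 1 year.

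This changes analysis and reporting wording only. It uses child age, which the trial already collects; the child-time version needs age in months. The baseline will look slightly less balanced. A restricted comparison loses about 16% of children (13.0% control, 18.6% intervention) and drops the infants the programme set out to include. Child-time or age bands are preferable on that ground.
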